## Abstract

**Background:**

SARS-CoV-2, a novel coronavirus strain, has resulted in the COVID-19 pandemic since early 2020. To contain the transmission of this virus, the Swiss Federal Council ordered a nationwide lockdown of all nonessential businesses. Accordingly, students and employees of institutions for higher education were informed to continue their academic programs through home-office settings and online lectures.

**Objective:**

This longitudinal survey aims to evaluate various lifestyle habits such as physical activity, nutritional habits, and sleep behavior among students and employees of a Swiss University of Applied Sciences during a 2-month period of confinement and social distancing due to the COVID-19 pandemic and 1 year thereafter.

**Methods:**

This paper describes a protocol for a retrospective and prospective observational cohort study. Students and employees of Bern University of Applied Sciences, Department of Health Professions, were invited to anonymously complete a web-based survey during the COVID-19 confinement period. This will be followed by a second survey, scheduled 1 year after the lockdown. Information on various lifestyle aspects, including physical activity, nutritional habits, and sleep behavior, will be collected using adaptations of existing validated questionnaires.

**Results:**

This longitudinal study started during the government-ordered confinement period in Switzerland in mid-April 2020 and will end in mid-2021.

**Conclusions:**

The findings of this survey will provide information about the impact of confinement during the COVID-19 crisis on the physical activity, nutritional habits, and sleep behavior of students and employees of a Swiss institute.

**Trial Registration:**

ClinicalTrials.gov NCT04502108; https://www.clinicaltrials.gov/ct2/show/NCT04502108

**International Registered Report Identifier (IRRID):**

DERR1-10.2196/25051

## Introduction

On March 11, 2020, the World Health Organization declared COVID-19 as a pandemic. Thereafter, on March 16, 2020, the Swiss Federal Council declared the pandemic as an extraordinary situation in accordance with the Epidemics Act from midnight of March 16, 2020, until April 19, 2020, during which stringent measures were introduced. All so-called “nonessential businesses” had to be closed, as well as schools of all levels, including universities and universities of applied sciences. The Swiss Federal Council called upon the members of the public to avoid all unnecessary social contact and to remain at home in order to maintain safe physical distance from other individuals, and as such, to contain the pandemic. This so-called extraordinary situation was extended further, and on May 11, 2020, most of the emergency packages were withdrawn.

These lockdown orders were immediately followed by the Head of the Bern University of Applied Sciences (BFH). Classroom teaching (ie, in lecture halls, classrooms, and skills rooms) was no longer possible, and students and employees were asked to remain at home and continue their work in home-office settings. During this period of confinement, social distancing, and working from home-office, lecturers were asked to switch to digital technologies to ensure continuation of various educational programs during the second half of the Spring 2020 academic semester and the upcoming Spring 2020/21 semester. The lifting of these strict COVID-19 measures is being closely monitored. The Swiss Federal Council can impose new restrictions in case of a sudden increase in new COVID-19 cases.

Lifestyle habits such as physical activity, nutritional habits, and sleep behavior of university lecturers and students during such an extraordinary period of confinement and social distancing have not been studied to date. However, there is ample evidence describing the positive effects of adequate physical activity as well as the negative effects of physical inactivity on human health [1-6]. During this nearly 2-month-long lockdown period, all sports infrastructure in Switzerland was forced to close. Although regular access to fitness clubs and sports facilities was no longer possible, individuals were allowed to continue walking, jogging, and cycling. Food shops, however, remained open during this confinement period, and Swiss residents were allowed to go outside for food supply while adhering to the recommended preventive measures (eg, maintaining safe physical distance). The positive relationship between healthy nutritional habits as well as good sleep behavior and improved human health has been well documented in the literature [7-9].

Because the COVID-19 pandemic is caused by a novel coronavirus strain, and vaccination and effective treatment options are currently lacking, it is difficult to predict how the pandemic will develop. Increased knowledge about lifestyle habits of students and employees of the Department of Health Professions (DHP) at BFH (BFH-DHP) during such an extreme confinement situation may help Heads and Deans of academic institutions to inform or counsel their students and employees during a similar situation, or in case of another outbreak, in the future. However, owing to the uniqueness of the ongoing COVID-19 crisis and its societal impact, such knowledge is currently lacking.

This longitudinal observational study will examine the impact of COVID-19 confinement on lifestyle habits such as physical activity, nutritional habits, and sleep behavior among students and employees of the BFH-DHP (Switzerland) during the 2-month confinement period and social distancing and 1 year after confinement.

## Methods

### Study Setting

This study follows a cohort study design and will be carried out at BFH-DHP in Switzerland. Figure 1 illustrates the flow diagram for the research design used in this study. This project is an interdisciplinary cooperation involving colleagues from the Departments of Nutrition and Dietetics and Physiotherapy of BFH-DHP. The contents of the survey will be developed at an interprofessional level.

This cohort study comprises 2 defined study periods: The first study period was in the end of April 2020, when the Swiss Federal Council declared the COVID-19 pandemic as an “extraordinary situation.” The first study was cross-sectional, consisting of an anonymous web-based survey. For the first survey, a questionnaire was sent to the staff and students of all 4 divisions of the institute during the COVID-19 confinement period. The participants’ responses were anonymous, in accordance with the data privacy policy of Switzerland [10]. Participants were not allowed to provide any personal information or other sociodemographic characteristics and living status. Participants could stop and exit the survey at any stage before completion. Anonymous survey procedures are known to yield higher disclosure rates of sensitive or stigmatizing information than nonanonymous procedures. Moreover, higher disclosure rates have traditionally known to be associated with more accurate results than lower disclosure rates [11].

**Figure 1 figure1:**
[figure not shown]
Flow diagram of the study.

The second survey will be conducted in May 2021; this survey will aim to collect information on the sociodemographic and living status of the participants. The time period for the first survey was 1 week and that for the second survey has been set to 2 weeks.

One researcher (SR) was responsible for the preparation of the electronic version of the first survey in April 2020 (during the full-confinement period); the same researcher will also complete implementation of the survey as a follow-up in May 2021. This study has been registered at ClinicalTrials.gov: NCT04502108.

### Ethical Approval and Consent to Participate

Prior to the planning of this protocol, the Dean of the Health Department of BFH was informed about the survey, and he approved this study. This cohort study will be performed following the ethical principles of the Declaration of Helsinki. In the introductory section of the survey, eligible participants (staff and students) were informed that the survey is voluntary and anonymous and that no medical data is requested. Participants could also contact the researchers for any information or further questions. Finally, participants were explicitly asked to provide informed consent for participation electronically, by clicking a button at the start of the electronic survey. The second survey will follow the same procedure outlined above. The evaluation system software we intend to use in this study does not allow for any tracing of the respondents.

The cantonal Ethics Committee of Bern is responsible for this research project. The main task of the ethics committees of Switzerland is to examine and approve applications for research projects in the field of human research. The committees evaluate projects that fall under the following definition from Article 2 of the Federal Act on Research involving Human Beings: “This Act applies to research concerning human diseases and concerning the structure and function of the human body, which involves: persons; deceased persons; embryos and foetuses; biological material; and health-related personal data.” We sought clarification from the Ethics Committee of Bern on whether this research project falls within the scope of the Human Research Act and/or to request a written statement in case the project does not need approval by the committee. We thus verified that this study does not need an approval from the ethics committee (Reference number: Kantonale Ethikkomission Bern, KEK Bern, Req-2020-00909).

### Recruitment

This cohort study aims to recruit at least 80% of the 1300 students and employees of BFH-DHP. The recruitment strategy comprised the following procedure: in consultation with and support of the director of BFH-DHP, an invitational letter will be sent via email to all students and employees during the first (April 2020) and second (May 2021) study periods.

### Eligibility Criteria

All students (N=1300; 88% female and 12% male) enrolled in programs at the Bachelor of Science and Master of Science levels as well as all academic and nonacademic employees of BFH-DHP are eligible and will be invited to participate in this comprehensive, web-based survey. BFH-DHP runs these educational programs in the fields of nursing, nutrition and dietetics, midwifery, and physiotherapy. Individuals that are not employed or enrolled at the university will not be eligible for this study.

### Outcomes

#### Primary Outcome (Physical Activity)

The validated German version of the international physical activity questionnaire-short form (iPAQ-SF) [12] will be used to assess the participants’ physical activity over the last 7 days. Seven items of the questionnaire will evaluate the number of days participants performed intensive and moderate physical activities and walking activities and the time (hours and minutes) spent per day in performing the exercises at those intensities. The primary outcome variable will be total physical activity expressed as metabolic equivalents of task in minutes per week (METs/week), which is calculated as the sum of 3 physical activities (ie, walking activity and moderate and intensive physical activities). For the categorical division into the 3 activity levels (low, moderate, and high), definitions from published evaluation guidelines will be used.

#### Secondary Outcomes

##### Nutritional Habits

The valid German version of the Mediterranean diet screener (bMDSC) [13] will be used to assess the participants’ nutritional habits and adherence to the Mediterranean diet. Participants will be asked to report their adherence to the recommended consumption frequency of 15 selected food items during the past year: (1) use of olive oil for cooking; (2) use of olive oil as salad dressing; (3) daily intake of cooked vegetables; (4) daily intake of raw vegetables; (5) daily intake of fruits; (6) daily intake of red meat or sausages; (7) intake of butter and bread for breakfast or dinner; (8) intake of soft drinks or sweetened drinks on the previous day; (9) attention to nutritional fiber intake; (10) weekly intake of legumes, chickpeas, and beans; (11) intake of fish 1-2 times per week; (12) consumption of nuts at least at 3 days per week; (13) preference of white meat over read meat; (14) intake of rice or pasta with vegetable sauce as part of the diet; and (15) consumption of French fries on the previous day [14]. Response categories will be “Yes” or “No.” All questions will be scored “1” if answered with “Yes,” except questions (6), (7), (8), and (15) that will be scored “1” if answered as “No.” Scores will be summed, and a higher score will indicate better adherence to the Mediterranean diet.

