##### Second Survey

The same questionnaire that was used in the first survey will be sent to all eligible staff and students of BFH-DHP about 1 year later (ie, Spring 2021) during the period of “new normality.” The survey will be open during a 2-week period, and automated reminders will be sent to all participants. Because the process will be completely anonymous, the question “Did you volunteer to participate in the same survey last year?” will be added to the questionnaire. This question will allow to extract a set of participants that filled out both surveys and further perform group comparison analyses of lifestyle habits during confinement and under conditions of “new normality.” Furthermore, the second survey will include additional questions on gross anthropometric characteristics (ie, height and weight), sociodemographic characteristics, living status, gender, age, household size, changes in smoking habits, and quality of life.

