#### Data Collection

This electronic survey will be conducted anonymously using the “evaluation system software” of BFH-DHP (EvaSys, Electric Paper EvaluationssystemeGmbH), which is typically used for quality control of lectures, seminars, and other educational products. The validated iPAQ-SF and bMDSC questionnaires will be transferred within the EvaSys-framework to assess participants’ physical activity and nutritional habits. Additional questions on alcohol consumption and sleep behavior will also be added to the survey.

The first survey will be conducted electronically. After closing of the 1-week survey period by the end of April 2020, the data collected will be merged and automatically extracted into an Excel spreadsheet for further analyses. The first survey will be analyzed as a cross-sectional study, in accordance with the official guidelines to analyze iPAQ-SF and adapted bMDSC. The survey results will be subjected to analyses as described in the Statistical Analyses section.

The second survey in May 2021 will also be analyzed as a cross-sectional study using the same procedures as used for the analysis of the first survey in 2020. In addition, a subgroup analyses of participants who volunteered in both surveys will allow for group comparison (during confinement versus after confinement).

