## Results

This longitudinal study was started during the lockdown in Switzerland, in mid-April 2020 and will be completed in May 2021. The first phase of the study is underway, and data from 823 participants will be evaluated.

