## Discussion

This paper outlines the study protocol of the survey conducted among BFH-DHP students and employees to evaluate their physical activity, nutritional habits, and sleep behavior during the 2020 COVID-19 confinement. This protocol has been developed as an interdisciplinary collaboration between faculty members of the Divisions of Nutrition and Dietetics and Physiotherapy.

During the same period, similar initiatives were undertaken by other institutes. For example, a large survey developed by a consortium of many international universities aimed to retrospectively evaluate the changes in lifestyle habits among the general population in context of the COVID-19 pandemic [2,15,16].

One of the strengths of our survey is that it will be short (time needed to complete the survey will be less than 10 minutes), limiting the questions to physical activity, nutritional habits, and sleep behavior within a specific setting of students and employees of BFH-DHP. We believe, this will help the participants place special focus on the current and future multipliers of healthy lifestyle habits and their own personal behavioral changes due to a general lockdown effected as a key countermeasure to combat the spread of the COVID-19 pandemic. Another strength of our survey is its prospective design over a 1-year period. Based on the large sample size comprising eligible staff and students (N>1500) and considering the huge impact of COVID-19–related strict measures on both the staff and students, we expect a reasonable response rate (ie, around 30%).
It may be hypothesized that such a confinement period may negatively affect physical activity levels of individuals, in general, and students and employees of BFH-DHP, in particular. In an effort to support the public in maintaining “healthy” physical activity levels, Swiss television channels resumed broadcasting home exercise programs after almost two decades. During this time, popular press reported an increase in the demand for fresh vegetables and fruit, as well as alcoholic beverages. Our survey will aim to verify and, if applicable, quantify such observations and put them in proper context.

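### The diet score's past-year recall frame conflicts with its use as the confinement measure: for 13 of its 15 items only about 10–12% of the recall year falls in lockdown

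*Protocol article*

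**What the plan says.** The Nutritional Habits section defines the diet outcome as the sum of 15 Yes/No items on adherence to the "recommended consumption frequency of 15 selected food items during the past year". Two items carry a different period in their own wording: item 8 ("intake of soft drinks or sweetened drinks on the previous day") and item 15 (French fries, also the previous day). All 15 go into one score.

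The intended use is stated elsewhere. The abstract's Objective names nutritional habits among the behaviours to be evaluated over the two months of confinement and one year later. The First Survey section says the survey was kept to one week so that it would be a snapshot of full confinement. The Second Survey section plans "group comparison analyses of lifestyle habits during confinement" against the situation a year later, using the same questionnaire, and Data Collection repeats that contrast. Statistical Analyses adds a comparison with pre-COVID-19 values from the general population. The Discussion, after mentioning press reports of higher demand for vegetables, fruit and alcohol, says "Our survey will aim to verify and, if applicable, quantify such observations".

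The primary outcome, physical activity, is asked over the last 7 days.

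**The concern.** A question about the past year, answered a few weeks into a lockdown, is mainly a question about life before the lockdown. If the score is then labelled as diet during confinement, three planned uses are affected:

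- **2020 versus 2021.** The contrast is presented as during versus after confinement. With past-year frames it is mostly a pre-lockdown year against the year that followed the lockdown.
- **2020 versus pre-COVID-19 reference values.** A score that itself reaches back mostly before the pandemic will tend to hide a confinement effect. A null result could be misread as showing that confinement left diet unchanged.
- **The food part of the Discussion aim.** The vegetable and fruit items (3 to 5) carry the past-year frame, so they are poorly placed to confirm or quantify a change that began in March 2020.

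Diet is a secondary outcome, but it is one of the three behaviours named in the objective and the conclusions. The second survey and the reporting still lie ahead, so the labels can be put right.

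**Working it through.** The document gives no figure for this share, so there is nothing to reproduce. The check is calendar arithmetic.

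**Inputs**
- Start of confinement (Introduction): "from midnight of March 16, 2020, until April 19, 2020, during which stringent measures were introduced". I count from 16 or 17 March 2020.
- End of confinement (Introduction): "on May 11, 2020, most of the emergency packages were withdrawn".
- First survey (Data Collection): "After closing of the 1-week survey period by the end of April 2020". A one-week window closing on 30 April opens on 24 April. The Results section dates the study start earlier: "This longitudinal study was started during the lockdown in Switzerland, in mid-April 2020". I therefore also try 15 April.
- Recall frame: past year, which is 366 days looking back from April 2020 because it contains 29 February.
- Second survey: May 2021, with a look-back of 365 days.

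**Survey 1, year-frame items.** Confinement share = (days from start of confinement to survey) / 366.

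| Survey date | Confinement days | Confinement share | Pre-lockdown share |
|---|---|---|---|
| 15 April 2020 | 29–30 | 7.9–8.2% | 91.8–92.1% |
| 24 April 2020 | 38–39 | 10.4–10.7% | 89.3–89.6% |
| 30 April 2020 | 44–45 | 12.0–12.3% | 87.7–88.0% |

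As an upper bound, even a survey on 11 May 2020 would give at most 56 / 366 = 15.3% in confinement. The exact survey date does not change the picture.

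**Survey 1, whole score.** Items 8 and 15 refer to the previous day, so they fall inside confinement. Treating items as equal parts of the score, the pre-lockdown part is (13 / 15) × pre-lockdown share:
- 24–30 April: (13 / 15) × 87.7% = 76.0% up to (13 / 15) × 89.6% = 77.7%.
- 15 April: up to (13 / 15) × 92.1% = 79.8%.

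About 76–80% of the score's content thus refers to the time before lockdown.

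**Survey 2, year-frame items.** Confinement days are those in the window before 11 May 2020:
- Survey on 1 May 2021: 10 / 365 = 2.7%.
- Survey on or after 11 May 2021: 0 / 365 = 0%.

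**Contrast with the primary outcome.** A 7-day look-back from 24 April starts on 17 April, wholly inside confinement. The activity frame fits the objective and the diet frame does not.

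**The case against.** The strongest reply is that the wording sent in April 2020 is not shown. The abstract's Methods speak of adaptations of validated questionnaires, and Data Collection speaks of an adapted diet screener. The recall period may have been shortened. This stands: the document does not prove that the data already collected are mostly pre-lockdown. It does show that the stated frame conflicts with the stated use, and no section says the window was changed.

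A second reply is that day counts do not translate into answers. This also stands. A reader might infer from the 10–12% share that only about a tenth of a real dietary change would reach the score, or that the change is almost wholly lost. The document does not support that. The score is a sum of Yes/No answers, and a respondent who changes a habit in March either switches the answer or does not. Respondents may also give recent weeks more weight. The size of any dilution cannot be determined from the document. The same holds for the inference that the 2020–2021 difference would change sign: this is conceivable, but no figure in the document bears on it.

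Third, previous-day items are listed as part of a validated instrument, several others (for example attention to fibre, preference for white meat) read as current habits, and the correlation analysis is labelled exploratory. These are fair points. Mixing reference periods in one score, and pairing past-year diet with 7-day activity, are limits on interpretation rather than errors in themselves.

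Fourth, the Discussion aim is wider than diet. A reader might infer that the whole aim fails, but activity is asked over 7 days and alcohol in units per day, so neither is touched by the past-year frame.

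**Conclusion.** The concern holds as a conflict between the diet score's stated recall frame and its stated use. For the 13 year-frame items, 10–12% of the recall year at the April 2020 survey lies in confinement (about 8% for a mid-April survey). For the May 2021 survey the share is 0–2.7%. The planned diet contrast is therefore mostly a pre-lockdown year against the first pandemic year. In the comparison with reference values, any confinement effect is likely pulled toward no difference by an unknown amount.

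This rests on two assumptions: that the questionnaire used the frame the article states, and, for the percentages, that each day of the window counts equally. The percentages describe the recall window and are not an attenuation factor. The primary outcome is not affected.

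**What to change.** First check the questionnaire that was sent in April 2020.

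- **If it used a shorter frame,** correct the Nutritional Habits section to that wording. The conflict is then resolved to the extent that the frame lies within confinement.
- **If it used the past-year frame:**
  1. Label the 2020 score as usual diet, predominantly before confinement, and the 2021 score as diet in the first pandemic year.
  2. Drop the during-versus-after-confinement interpretation for the sum score, and state the same caveat for the comparison with pre-COVID-19 reference values.
  3. Report items 8 and 15 separately, as the diet items that in 2020 refer to days in confinement.
  4. In the Discussion, withdraw the aim of verifying the reported demand changes for vegetables and fruit only. Keep it for activity and alcohol.

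Short-frame diet items added to the second survey would have no 2020 counterpart and could not restore the comparison, so they are not part of this fix. The cost is a wording change and a narrower conclusion on diet, with no new data collection.
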